
## Methods

### Study Design and Setting

This cohort study is implemented in a single center and applies a pre-post mixed methods (qualitative-quantitative convergent) design. Participants are recruited from Prevention and Early Intervention Program for Psychosis (PEPP)–Montreal, the Douglas Mental Health University Institute in Montreal, Quebec. This program provides a comprehensive range of services for young people diagnosed with FEP and follows best practice guidelines for real-world settings [7,8]. Treatment includes psychiatric evaluation and follow-up, modified assertive case management tailored to meet the needs of young patients in the early phase of illness [8] including support toward treatment goals (eg, illness education, return to work or school, and crisis intervention), family support and intervention, and psychosocial group interventions (eg, physical, recreational, recovery, and support).

### Participants, Sample Size Considerations, Recruitment, and Orientation Process

The target sample is 20 to 25 participants that are patients receiving services from PEPP-Montreal. This sample size was determined by the following factors: feasibility of participant recruitment within a 2- to 3-month time frame, budget related to staffing of moderators, and ensuring adequate number of active users on the platform for the social networking features to function effectively. This sample size has also shown to be sufficient to pilot-test the feasibility and acceptability of Horyzons, as illustrated in the prior pilot study [27] while also acknowledging the limitation of this small sample size for efficacy testing (which is not the main objective of this pilot study). Participant inclusion and exclusion criteria are presented in Textboxes 1 and 2, respectively.

Inclusion criteria.
**Participants**
Diagnosis of a psychotic disorder (including affective or nonaffective psychoses) by a clinicianReceiving specialized services for a first-episode psychosis at the recruitment siteConsidered symptomatically stable and capable of interacting on the online platform and participating in focus groups and semistructured interviews, as judged by their primary clinicians (ie, psychiatrist, case manager)18 years or olderAt low or at most moderate severity score (4 or below) on the suicidality item of the Brief Psychiatric Rating Scale, version 4 [46] for the month preceding study entry. This criterion is to minimize risk for the need of urgent intervention regarding comments pertaining to suicidal ideation and plans posted on the social network or to the moderation team (given that the platform is not monitored 24/7) and to reduce potential anxiety or distress in other participants from overexposure to content focused on suicide.Able to nominate an emergency contact

Exclusion criteria.
**Participants**
Intellectual disabilityHospitalized at the time of recruitmentUnable to speak or read EnglishDiagnosis of antisocial personality disorder or borderline personality disorderIn the acute phase of mania or psychosis to the extent that their mental status may soon require hospitalization or would impede the participant’s ability to provide informed consent or to participate in interviews and focus groups

In terms of the recruitment process, a member of the research team met with clinicians at the recruitment site to describe the project, including the rationale, objectives, inclusion and exclusion criteria, and methods. The treating clinicians screened all participants. The treating clinicians referred patients who fulfilled the aforementioned inclusion and exclusion criteria. The treating clinicians provided a copy of the study information handout to prospective participants when introducing the study so that they had time to consider the study and ask questions about it. Once participants completed screening for eligibility, were identified as being eligible to participate, and expressed interest to learn more about the study, they were contacted by a member of the research team to receive further details about the project, their participation, and the informed consent process. A study information brochure was provided to participants as a summary of the information contained in the consent form for user-friendly access to key information about the project.

Participants received detailed information concerning their participation including date, time, and duration of scheduled meetings, interviews, and activities related to study participation. In addition, they were contacted 24 hours prior to any scheduled interviews to confirm their participation. They were contacted according to their preferences either by phone, e-mail, or in person when attending the clinic. After providing written informed consent, the research assistant administered the baseline measures, the results of which were also used to confirm clinical stability and eligibility to participate. In a subsequent HoryzonsCa Orientation Meeting, participants were oriented to the HoryzonsCa website and provided with login information. Participants were then able to access the website, at their convenience, over a period of 8 weeks. They were encouraged to log into the website at least 1 time per week for a minimum of 15 minutes per visit. Access to HoryzonsCa was in addition to the services that participants already receive from PEPP-Montreal. The Horyzons safety protocol [27] was adapted for this study and included an assessment procedure for risk of suicide attempt. This assessment has been implemented by members of the team in the context of other psychosocial intervention research projects with the same clinical population. All research team members were trained in the safety protocol. Given that it was the first time the website and safety protocol was used in a Canadian context, the results of this study will help identify potential modifications to improve the safety protocol for future research on HoryzonsCa. The details of the adapted safety protocol and withdrawal criteria are provided in Multimedia Appendix 1.

### Data Collection

We collected quantitative and qualitative data through interview-based psychometric measures, self-reports, focus groups, and interviews. An initial interview consisted of completing a self-reported sociodemographic questionnaire, the Technology Access, Use, and Competency Questionnaire (TAUC-Q), and a combination of self-reported and interviewer-administered clinical measures (for social functioning, global improvement and therapeutic response, social support, self-esteem and perceived strengths, and symptoms). The TAUC-Q and the clinical measures were also administered during the exit interview at the 8-week follow-up along with the interviewer-administered Horyzons-Canada Acceptability, Usability, Safety, and Impact Questionnaire (HC-AUSI-Q). Participants were also invited to a HoryzonsCa Meet-up and Focus Group during the follow-up period. Multimedia Appendix 2 provides an overview of the schedule of assessments that took place across the duration of the follow-up.

### Outcome Measures

#### Sociodemographic Characteristics and Access and Use of Technology

Participants were asked to complete a sociodemographic questionnaire (self-report) consisting of nine questions regarding gender, age, length of service use, highest level of education completed, ethnicity, vocational status, living situation, marital status, and annual income. Participants’ access, use, and attitudes in relation to technology was assessed using the TAUC-Q (self-report), which includes 10 questions regarding participants’ access and use of internet and mobile technology (eg, smartphone, computer, social media, text, or email) and perceived competency of technology. Their responses on these questionnaires will allow us to estimate the transferability of our results and to better understand participant experiences, use, and perceptions of the platform.

#### Acceptability

*Acceptability* (TAM components of perceived ease of use and perceived usefulness) was measured through the HC-AUSI-Q and website use analytics. The HC-AUSI-Q is an adaptation of questionnaires used in the HoryzonsCa phase 1 adaptation study [30,31], the Horyzons Usability Questionnaire from the original Horyzons pilot study [27], and the Website Analysis and Measurement Inventory [47]. The interviewer-administered HC-AUSI-Q consists of a questionnaire and a semistructured interview that includes 16 close-ended and 10 open-ended questions on perceived ease of use, perceived usefulness, enjoyment, and safety. The questions pertaining to acceptability address the topics of general experience (eg, “I had a positive experience on Horyzons-Canada”), usefulness (eg, “Horyzons was useful to identify my warning signs for relapse”), and ease of use (eg, “Overall, the platform is easy to use”). Acceptability in terms of adoption was assessed using website use analytics (eg, frequency of log-ins and patterns of use over 8 weeks).

#### Safety

*Safety*, which considers 3 levels of security (ie, online safety, clinical safety, system security), was assessed using two specific questions (ie, “I felt safe on Horyzons-Canada” and “I felt like the information shared on Horyzons-Canada was confidential”) in the HC-AUSI-Q. In addition, any adverse events, reports, or incidents (eg, hospitalization, suicidal ideation, or disclosure to treatment team regarding harm) in relation to the use of the online system were carefully monitored and quantified over the study duration. The causal relationship between adverse events and use of HoryzonsCa was determined based on detailed documentation of each event and through discussion by members of the research and moderation team. All adverse events, reports, and incidents (eg, hospitalization, major deterioration in ability to function) were also submitted to the ethics review board for further examination.

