Clinician moderators provide guidance, monitor clinical status, and ensure safety of the social networking environment. Clinician moderators develop brief case formulations that are presented at weekly supervision meetings with the senior clinical research team. Clinician moderators send each youth tailored content suggestions (eg, step or action) weekly based on the young person’s needs, interests, and strengths. Suggestions appear on the young person’s home page, and they receive a text notification via the intervention platform’s SMS text messaging feature. Peer support moderators are young adults with lived experience who have received peer support training and who have been stable and in remission for a minimum of 2 years. Their role includes assisting with orientation to the Horyzons intervention platform, providing support, and fostering engagement. For example, peer support moderators reach out to new users or users that have not logged into the intervention platform after a week. They also post *icebreakers* and comments, *like* the posts of users, and engage in role modeling activities. They receive supervision from the clinical research team. The integrity of the moderation is ensured through a detailed moderation manual, and all moderators participate in weekly to biweekly group supervision sessions with senior members of the team. The intervention platform includes a comprehensive safety protocol following best practices in internet research involving vulnerable people [28], which considers 3 levels of security (ie, online safety, clinical safety, and system security). This safety protocol (including criteria and the process for withdrawal from the study) was successfully used in previous research on Horyzons [27,29].

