HoryzonsCa will be acceptable to patients. Our conceptualization of acceptability is partially informed by the TAM [37,38], which posits that attitudes toward using a technology influence intention (“acceptance”) to use a technology, which is a direct determinant of behavior [37,38]. The attitude construct is composed of perceived usefulness (an individual’s perception that using an information technology [IT] system will be helpful to them) and perceived ease of use (an individual’s perception that using an IT system will be free of effort) [38]. Patients’ acceptance regarding the use of technologies in health care delivery has been extensively assessed using the TAM model and its derivatives, which highlight the importance of considering factors beyond the individual’s attitudes [41-44]. As such, we also include the concept of adoption in our conceptualization of acceptability, which “is defined as the intention, initial decision, or action to try or employ an innovation or evidence-based practice” [45]. Thus, using this combined understanding of acceptability, in this study, the intervention will be considered acceptable if at least 70% of participants provide positive reports on general experience of the platform, 60% provide positive reports on perceived usefulness (helpfulness), 60% provide positive reports on ease of use, and 60% log onto the site at least 4 times over the 8-week follow-up. These percentages are hypothesized based on the results obtained from the original Horyzons pilot study [27]. We will also determine acceptability through qualitatively assessing perceptions of HoryzonsCa in relation to likes, dislikes, perceived barriers and facilitators to using the platform, and ease of use/experiences of navigating and using its key features (eg, various psychoeducational modules or café) and through exploratory analysis of website use analytics.To assess the safety of the HoryzonsCa platform. *Secondary hypothesis:* HoryzonsCa will be safe, defined as no adverse events, reports, or incidents (eg, hospitalization, suicidal ideation, or disclosure to treatment team regarding harm) related to use of the platform from baseline assessment to 8 weeks follow-up, and at least 70% of participants report that they agree or strongly agree with the perceived safety of the platform and perceived confidentiality of information shared on the platform. We will also determine safety through qualitatively assessing perceptions of the HoryzonsCa platform (eg, experiences, concerns).To assess the potential efficacy of the HoryzonsCa intervention/platform. *Secondary hypotheses:* Participants will show moderate to large improvements (Cohen *d*≥0.5) on measures of social functioning (Social and Occupational Functioning Assessment Scale; Personal and Social Performance Scale) and either improvement of 1 point or no deterioration on the Clinical Global Impression Scale, from baseline to 8 weeks follow-up, as our primary foci for assessing potential efficacy. We will also assess for improvements in social support, self-esteem and perceived strengths, and symptoms. The analysis will help determine pre-post effect sizes on a number of variables conceptually targeted by the platform. These effect sizes will be used in a future clinical trial (eg, randomized controlled trial) for the purpose of statistical power calculation and estimation of sample size.

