## Results

This study was funded by the Brain and Behavior Research Foundation (United States), Quebec Health Research Funding Agency (Canada), and the Canada Research Chairs Program (Canada), and was approved by the Research Ethics Board of the Centre intégré universitaire de santé et de services sociaux de l'Ouest-de-l'Île-de-Montréal on April 11, 2018 (#IUSMD 17-54). The study was registered as a clinical trial at [60] (ISRCTN43182105). Recruitment was initiated on May 10, 2018, and data collection occurred between August 16, 2018, to April 29, 2019. A total of 48 individuals were approached for the study, from which 20 were excluded (17 declined to participate, 1 was not reachable, 1 did not meet inclusion criteria, and 1 met exclusion criteria). The 28 remaining individuals provided informed consent and were invited to complete a baseline assessment, from which 4 did not attend for various reasons (eg, no longer interested, no longer attending clinic, or not feeling well). Among the 24 participants that completed the baseline assessment, 3 dropped out of the study before being given access to the intervention, and 1 was excluded from the intervention soon after team discussion of the baseline assessment due to not meeting inclusion criteria (ie, clinical stability). Upon completion of the baseline assessment and confirmation of eligibility criteria, a final sample of 20 participants were given access to the intervention and none of these were lost at 8 weeks follow-up. Participants were recruited over a 9-month duration (which was 3 times longer than our originally anticipated 3-month timeline), with a recruitment rate of approximately 3 participants per month. A total of 9 participants attended the focus group meetings of approximately 120 minutes each session (4 attended more than once). No adverse events related to the intervention occurred during the live pilot implementation. Further details on the results are expected to be submitted for publication in 2021.

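### The event part of the safety hypothesis counts only events that the study's own research and moderation team judges related, so the conclusion should show all events beside that count

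*Protocol article*

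**What the plan says.** Under Objectives and Hypotheses, the article sets a two-part rule. The event part reads "HoryzonsCa will be safe, defined as no adverse events, reports, or incidents", with hospitalization, suicidal ideation and disclosure of harm to the treatment team as examples. It is then restricted to those "related to use of the platform from baseline assessment to 8 weeks follow-up". The second part requires that "at least 70% of participants report that they agree or strongly agree with the perceived safety of the platform", and likewise for confidentiality. A qualitative look at experiences and concerns is added.

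Under Outcome Measures, Safety, the article says that events "in relation to the use of the online system were carefully monitored and quantified over the study duration". Causality was "determined based on detailed documentation of each event and through discussion by members of the research and moderation team". The same paragraph adds: "All adverse events, reports, and incidents (eg, hospitalization, major deterioration in ability to function) were also submitted to the ethics review board".

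The Results section states: "No adverse events related to the intervention occurred during the live pilot implementation". It gives no count of events irrespective of cause and says that further results will follow in a later publication.

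**The concern.** Relatedness here decides whether the event part of a stated hypothesis is met. It is not just a descriptive column in a table. The judgement is also made by an interested group. The Horyzons Intervention Platform section says that team members developed the platform, and of the moderators it says: "Clinician moderators provide guidance, monitor clinical status, and ensure safety of the social networking environment". Judging an event related may therefore amount to a judgement on the moderators' own work.

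The study has no control group, as Strengths and Limitations acknowledges. When a patient in early psychosis is hospitalized during the 8 weeks, nothing in the design can confirm or refute that the platform played no part. A conclusion stated only on the related count leaves the reader unable to see how much of it rests on attribution. Safety is one of three objectives, and the results are meant to inform a larger evaluation.

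**Working it through.** The article states no rate, power or sample-size figure for safety, so there is none to reproduce. The check has two parts.

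**1. Logic of the rule.** Suppose one of the 20 participants is hospitalized in week 5.

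- Team judges it related: the event part fails.
- Team judges it unrelated: the event part is met. The hypothesis then needs 0.70 × 20 = 14 favourable ratings on perceived safety and confidentiality. These items ask how participants felt about the platform and do not register the hospitalization.
- Ethics board: it receives the event, but the article does not say that it rules on relatedness or can alter the verdict.

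**2. How often attribution could matter (illustration only).** Inputs: 30% relapse (Introduction, Background, no period given); 8 weeks of access; 20 participants with access, none lost (Results). Assumptions: constant hazard, independence between participants, and a period of *T* years for the 30%.

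- 8-week risk: p = 1 − 0.7^(8/(52T))
- Chance of at least one relapse among 20: 1 − (1 − p)^20

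| Assumed period T | p | Expected relapses, 20p | Chance of at least one |
|---|---|---|---|
| 1 year | 5.3% | 1.07 | 67% |
| 2 years | 2.7% | 0.54 | 42% |
| 5 years | 1.1% | 0.22 | 20% |

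Entry required clinically judged stability and a limit on the suicidality score, so the true figures are probably lower. Relapse is also not identical to the events listed in the hypothesis.

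The effect of attribution can be shown separately. Let p now be an assumed all-cause event risk per participant and r the share of affected participants whose event is judged related. The chance of meeting the event part is (1 − p·r)^20:

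| Assumed p | All judged related (r = 1) | Half (r = 0.5) | None (r = 0) |
|---|---|---|---|
| 5% | 35.8% | 60.3% | 100% |
| 10% | 12.2% | 35.8% | 100% |
| 20% | 1.2% | 12.2% | 100% |

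At a fixed true event risk, the result moves across each row through r alone.

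**The case against.** The other side has several fair points.

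- **The rule is joint.** A reader might infer that relabelling an event is enough to produce a verdict of safe. It is not: the 70% condition must also hold. This stands and limits the point to the event component.
- **There is outside scrutiny.** All events went to the ethics board, and the adapted safety protocol in Multimedia Appendix 1, which is not shown, may contain attribution criteria. This stands to the extent that missing criteria cannot be held against the article. It does not connect the board's review to the verdict.
- **The Results sentence is a preview.** A reader might infer that the all-cause count will never be reported. Nothing says so, and the article announces a fuller report.
- **Some attribution is defensible.** On the illustration above, a standard of zero events from any cause would fail through background illness alone in 20% to 67% of such studies, before allowing for selection. Attribution by the study team is also a common arrangement. This stands and is a reason to keep the criterion.
- **This is a small pilot and safety is a secondary hypothesis.** The authors already urge caution, citing the short follow-up. This lowers the severity, but that caution does not address who judges relatedness.

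**Conclusion.** The point holds for the event component of the safety hypothesis. As stated, that component can be met despite hospitalizations or suicidal ideation during access if the research and moderation team judges them unrelated, and the other component would not pick them up.

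The size cannot be fixed from the article. The 67%, 42% and 20% figures depend wholly on an assumed relapse period, a constant hazard and no allowance for selection. They show only that a background event in 20 people over 8 weeks is plausible.

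A reader might go further and infer that events were misclassified or that the reported result is wrong. The article does not support that: it shows neither that any event occurred nor that one was wrongly attributed. This is a should-fix point about how the safety conclusion is built and reported.

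**What to change.** Keep the prespecified related-event criterion. Data collection has ended and the related-event result is already stated, so replacing the definition now would be a post hoc change. Beside it:

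1. Tabulate all adverse events, reports and incidents in the 20 participants with access, by type, number of participants and number of events, whatever the attribution.
2. Give relatedness as a second column and state who judged it. The article gives neither the ethics board nor the treating clinicians that role, so it should not be ascribed to them.
3. Word the conclusion on both counts: *x of 20 had any event, y judged related by the study team*.

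The records should already exist, since the article says that all events were submitted to the ethics board. The cost is one extra table and a changed sentence. The downside is that the safety result may look less favourable.
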